### Sample Size Calculation

The calculation of the required sample size was conducted within the framework of an exploratory study. The required number of patients was set to 200 based on a statistical power of 80% with a type I error rate of 5% and theoretical percentages of AF incidence of 10% for the group of patients considered moderately exposed (<75th percentile of the average heart radiation dose distribution) and 25% for the group of patients considered highly exposed (>75th percentile of the average heart radiation dose distribution) [60]. We plan to include these 200 patients in approximately 30 months.

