### Outcome Measurement

#### Primary Outcome

The difference in the occurrence of AF (questionnaire + SL-ECG based) throughout the 5-year follow-up after RT according to heart exposure (moderate or low exposure: <75th percentile of radiation dose distribution for the whole heart; and high exposure: ≥75th percentile of radiation dose distribution) will be measured as the primary outcome of interest for this study.

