### Planned Statistical Analysis

We will summarize the baseline data (description of the cancer and treatments, history of cardiovascular diseases, cardiac dosimetry) using descriptive statistics: means (SDs) will be used for continuous data with a normal distribution, medians (IQRs) for skewed data, and percentages for categorical data. Continuous data will be compared between cases and noncases of AF using the *t* test or the Wilcoxon Mann-Whitney test, and categorical variables will be compared using the chi-square test. All tests will be bilateral, with α=5%.

The estimation of the incidence of AF and other cardiovascular pathologies occurring in the 5 years following RT will be carried out based on data collected during the cardiology consultation (SL-ECG screening, 12-lead ECG, and echocardiography) and the medical questionnaire. A univariate analysis using regression models will identify the risk factors associated with the studied cardiovascular pathologies, other than cardiac radiation exposure (ie, individual and medical characteristics). Subsequently, only variables with *P*<.20 will be retained for multivariable analyses [61]. Estimations of the risk of AF and other cardiovascular diseases according to cardiac radiation doses will be performed using regression models adjusted for the risk factors identified in the univariate analysis. To limit issues in the multivariate analysis due to correlation between dosimetry parameters, each dosimetry parameter will be analyzed separately. Analysis will be performed using the data analysis and statistical software SAS version 9.4.

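### The stated 80% power for 10% vs 25% does not hold at the roughly 150/50 split that the 75th-percentile cut produces; under two-sided testing it is about 73%

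*Protocol article*

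**What the plan says.** Four places in the protocol article bear on this point.

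- **Sample Size Calculation** (Methods): "The required number of patients was set to 200 based on a statistical power of 80% with a type I error rate of 5" percent. The planning rates are AF incidence of 10% below the 75th percentile of mean heart dose and 25% above it. The section places the calculation in an exploratory framework. It gives no formula, allocation ratio or sidedness.
- **Primary Outcome** (Methods): the primary comparison uses the same cut, "moderate or low exposure: <75th percentile of radiation dose distribution for the whole heart", against the 75th percentile and above.
- **Planned Statistical Analysis** (Methods): "All tests will be bilateral, with α=5" percent. Categorical variables are compared with the chi-square test.
- **Abstract, Results**: the same 200 patients and 80% power are tied to AF incidence of around 15% and 25%, not 10% and 25%.

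**The concern.** A 75th-percentile cut divides a cohort into three quarters and one quarter. For a fixed total, a 3:1 split estimates a difference less precisely than equal groups do, so a total that gives 80% power with equal groups gives less here. The stated total is exactly the equal-group answer, which suggests that the split was not carried into the calculation.

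The power statement supports the between-group comparison named as the primary outcome. If true power is about 73%, the type II error is about 27% instead of 20%, even when every planning assumption is right. A non-significant result would then be read as stronger evidence against a dose effect than the design can supply.

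**Working it through.** **Inputs.** Total 200, power 80%, type I error 5%, p1 = 0.10, p2 = 0.25 (Sample Size Calculation). Cut at the 75th percentile (Primary Outcome and Sample Size Calculation). Two-sided tests (Planned Statistical Analysis). Hence z = 1.960 for the type I error and 0.842 for 80% power.

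**Step 1: reproduce the plan's figure.** The pooled two-proportion formula with equal groups has mean rate (0.10 + 0.25)/2 = 0.175:

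n per group = [1.960·√(2·0.175·0.825) + 0.842·√(0.10·0.90 + 0.25·0.75)]² / 0.15² = (1.053 + 0.443)² / 0.0225 = 99.5, rounded up to 100.

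The total is 200, and power at 100/100 is 80.2%. The plan's figure is reproduced, but only with equal groups.

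**Step 2: apply the plan's own split.** 0.75 × 200 = 150 and 0.25 × 200 = 50.

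- Mean rate = (150·0.10 + 50·0.25)/200 = 0.1375
- SE under the null = √[0.1375·0.8625·(1/150 + 1/50)] = 0.0562
- SE under the alternative = √(0.09/150 + 0.1875/50) = 0.0660
- Power = Φ[(0.15 − 1.960·0.0562)/0.0660] = Φ(0.603) = 72.7%

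**Step 3: check that the result does not depend on the formula.** All rows are for 150/50, 10% vs 25%, two-sided 5%.

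| Method | Power |
|---|---|
| Chi-square, exact enumeration | 73.5% |
| Log odds ratio, Wald | 73.4% |
| Pooled normal formula | 72.7% |
| Arcsine | 69.6% |
| Fisher exact | 68.6% |
| Continuity-corrected chi-square | 65.6% |
| Unpooled normal approximation | 62.3% |

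No method comes within 2 points of 80%. The uncorrected chi-square is the most favourable to the plan.

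**Step 4: what 80% would take at 3:1.** n in the larger group = [1.960·√(0.1375·0.8625·4) + 0.842·√(0.09 + 3·0.1875)]² / 0.15² = (1.350 + 0.680)² / 0.0225 = 183.1, rounded up to 184. With 62 in the smaller group the total is 246. If the total stays at 200, the upper rate detectable with 80% power against 10% is 26.8%, or about 27%.

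**Step 5: the other route to about 200.** A one-sided 5% test at 3:1 needs 147 + 49 = 196 patients, and 150/50 then gives 80.8%.

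**Step 6: the abstract's rates.** For 15% vs 25%, two-sided 5%, power is 37.5% at 150/50 and 42.3% at 100/100. Neither split supports 80%.

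**The case against.** **The cause is not documented.** This stands. The article states no formula and cites a reference that is not available here. The authors may have allowed for the 3:1 split and used a one-sided test, which also leads to about 200. That reading conflicts with "All tests will be bilateral" in Planned Statistical Analysis, and power under the planned two-sided test is about 73% either way. The shortfall therefore does not rest on the equal-group explanation.

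**The percentile might come from an outside dose series.** The article does not say whose distribution is meant, so 150/50 is the natural reading but not a certainty. It matters little: with 30% of patients in the high-dose group (140/60), power is still only 76%.

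**The study is exploratory.** The article says so, and its Limitations section acknowledges a small sample. This can justify accepting lower power and it lowers the severity. It does not make the stated figure correct.

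**Stronger readings that the article does not support.** A reader might infer further loss of power from the smartwatch wear adherence quoted in the Introduction (73%, falling to 63% at day 30). Those figures come from another trial and are cited to support a one-month wearing period. They are not proportions of patients without an outcome, because the primary outcome also uses the questionnaire, which is checked against medical records. Nor is the lack of a stated dropout allowance a finding, since a condensed article commonly leaves that to the full protocol. A reader might also set the 8.6% AF incidence cited for older patients with breast cancer against the planning rates. That figure comes from a review of other studies, and the article argues that most earlier studies under-captured AF. Planning on a higher rate fits that argument.

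**Conclusion.** The Sample Size Calculation is wrong as written. With 200 patients divided at the 75th percentile of their own mean heart dose, AF of 10% vs 25% and a two-sided 5% test, power is about 73%, roughly 7 points below the stated 80%. Reaching 80% would need about 246 patients. This rests on three things: the percentile belongs to the study's own distribution, the comparison is the unadjusted two-group one that the planning rates describe, and all 200 patients contribute an outcome.

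The abstract's claim fails by more (about 37%) and also contradicts the Methods on the lower rate. The article does not show which lower rate was intended.

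A reader might conclude that equal allocation was demonstrably assumed, or that the study must be enlarged. The first is plausible but unproven. The second does not follow for a study declared exploratory, where an accurate statement of power is enough. The point should be fixed, but it does not invalidate the design.

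**What to change.** Keep 200 patients and make two changes.

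1. In Sample Size Calculation, replace the power statement with wording such as: *With about 150 and 50 patients and a two-sided 5% test, power is about 73% for AF incidence of 10% vs 25%; the difference detectable with 80% power is 10% vs about 27%.* Name the formula and state that the percentile is taken from the study's own dose distribution.
2. In the abstract's Results, correct the 80% claim and reconcile 15% vs 25% with the 10% vs 25% in the Methods. If 15% was intended, the Methods paragraph must instead report about 37% power at 150/50.

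The cost is rewording one Methods paragraph and one abstract sentence. Recruitment, endpoint and analysis do not change. The stated power becomes less favourable. The article schedules data analysis from June 2026, and the correction is best made before then.

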### Planned Statistical Analysis

We will summarize the baseline data (description of the cancer and treatments, history of cardiovascular diseases, cardiac dosimetry) using descriptive statistics: means (SDs) will be used for continuous data with a normal distribution, medians (IQRs) for skewed data, and percentages for categorical data. Continuous data will be compared between cases and noncases of AF using the *t* test or the Wilcoxon Mann-Whitney test, and categorical variables will be compared using the chi-square test. All tests will be bilateral, with α=5%.

The estimation of the incidence of AF and other cardiovascular pathologies occurring in the 5 years following RT will be carried out based on data collected during the cardiology consultation (SL-ECG screening, 12-lead ECG, and echocardiography) and the medical questionnaire. A univariate analysis using regression models will identify the risk factors associated with the studied cardiovascular pathologies, other than cardiac radiation exposure (ie, individual and medical characteristics). Subsequently, only variables with *P*<.20 will be retained for multivariable analyses [61]. Estimations of the risk of AF and other cardiovascular diseases according to cardiac radiation doses will be performed using regression models adjusted for the risk factors identified in the univariate analysis. To limit issues in the multivariate analysis due to correlation between dosimetry parameters, each dosimetry parameter will be analyzed separately. Analysis will be performed using the data analysis and statistical software SAS version 9.4.

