**Results:**

Enrollment started in October 2023 and will continue until mid-2026 to include 200 patients, which will ensure an 80% statistical power to detect a significant difference in AF incidence around 15% for the group of patients moderately exposed (<75th percentile of the mean heart radiation dose) and 25% for the group of patients highly exposed (>75th percentile of the mean heart radiation dose). The results are expected by the end of 2026.

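### The dose models adjust for every factor with univariate P<.20 whatever the number of events, which costs precision and may bias the dose estimate modestly away from the null

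*Protocol article*

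**What the plan says.** Under Planned Statistical Analysis, univariate regressions look for individual and medical risk factors other than cardiac dose, and those reaching P<.20 go forward. Dose-risk estimates for AF and for other cardiovascular diseases "will be performed using regression models adjusted for the risk factors identified in the univariate analysis". Dose parameters are entered one at a time because they are correlated. That keeps the dose part of each model to one term, but it does not limit the covariates that each model carries.

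The Sample Size Calculation says "The required number of patients was set to 200", with "theoretical percentages of AF incidence of 10% for the group of patients considered moderately exposed" and "25% for the group of patients considered highly exposed". The groups are split at the 75th percentile of heart dose. The Results part of the Abstract gives a different lower rate: "a significant difference in AF incidence around 15% for the group of patients moderately exposed".

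The Summary in the Discussion names age, comorbidities and chemotherapy as confounders to be adjusted for. The analysis section does not fix them in the model.

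**The concern.** A screen at P<.20 lets through about one in five factors with no real effect, plus many of those with one. The more items the medical questionnaire and records supply, the more terms enter, while the number of events stays the same. With few events per parameter, maximum-likelihood logistic regression gives noisier coefficients, tends to push them away from the null, and sometimes fails to converge. The adjusted dose estimates are meant to point to high-risk cardiac regions and to inform RT delivery, so their precision and size matter. The same rule governs the secondary cardiac outcomes, for which no event counts are given.

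**Working it through.** **The plan's own figure.** With 10% v 25%, two-sided 5% and a 150/50 split, the pooled rate is (15 + 12.5)/200 = 0.1375.
- Null SE = √(0.1375 × 0.8625 × (1/150 + 1/50)) = 0.0562.
- Alternative SE = √(0.09/150 + 0.1875/50) = 0.0660.
- Power = Φ((0.15 − 1.96 × 0.0562)/0.0660) = 72.7%.

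The stated 80% is not reproduced at this split. Equal groups of 100 give 80.2%. That is a separate matter, but it shows there is little precision to spare.

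**Events.**
- Sample Size Calculation rates: 150 × 0.10 + 50 × 0.25 = 27.5.
- Abstract rate: 150 × 0.15 + 50 × 0.25 = 35.
- Implied dose OR from 10% v 25%: (0.25/0.75)/(0.10/0.90) = 3.0.

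**Events per parameter** = events/(factors kept + 1 for dose), taking each factor as one term. The number of candidates is not in the text shown, so 10 to 30 is assumed.
- If no candidate has a real effect, 20% pass. Ten candidates give 27.5/(2 + 1) = 9.2, and thirty give 27.5/(6 + 1) = 3.9.
- If 4 to 8 candidates are real (OR 1.5 each, independent), the simulation below gives 5.6 down to 2.6.
- At 35 events, with the same factors kept, each figure is 35/27.5 = 1.27 times larger.

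**Simulation of the stated rule.** 200 women, 50 highly exposed, true dose OR 3.0, about 27.5 events, logistic model assumed, 800 to 1,500 data sets per setting. The SE of the dose log OR without covariates is 0.44.

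| Candidates | Factors kept (mean) | Events per parameter | Mean adjusted OR | Bias | SE of log OR |
|---|---|---|---|---|---|
| 10 | 3.9 | 5.6 | 3.03 | +1% | 0.48 |
| 15 | 5.3 | 4.3 | 3.11 | +4% | 0.50 |
| 20 | 6.7 | 3.6 | 3.06 | +2% | 0.52 |
| 30 | 9.6 | 2.6 | 3.36 | +12% | 0.56 |

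A repeat simulation with 10, 20 and 30 candidates gave 3.12, 3.26 and 3.37 (+4%, +9%, +12%). Simulation error is about 0.52/√800 = 0.018 on the log scale, so biases of 1% to 2% cannot be told from zero. Coverage of the 95% interval was 94% to 95%. With no true dose effect and 20 candidates, the mean OR was 0.93 and coverage 97%.

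For precision, the ratio of the upper to the lower 95% limit is exp(2 × 1.96 × SE). It is 5.6 at SE 0.44, 6.6 at 0.48 and 9.0 at 0.56.

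**Rarer outcomes (event counts assumed).**
- About 14 events: OR 3.10, 3.28 and 3.65 for 10, 20 and 30 candidates (+3%, +9%, +22%). The SE rises from 0.60 to between 0.66 and 0.80. Failed fits were below 1% at 20 and 30 candidates.
- About 8 events, 15 candidates: OR 3.36 (+12%). The SE rises from 0.81 to 0.95, and 4% of fits failed or gave extreme values.

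**Firth penalisation on the same selected factors.**
- About 27 events: mean OR 2.84 to 2.95, with the SD of the log OR falling from 0.52–0.57 to 0.48–0.49.
- About 14 events: mean OR 2.94 to 3.01, SD from 0.73–0.93 to 0.63–0.71.
- Repeat simulation, about 27 events: OR 3.04 to 3.09. Root-mean-square error of the log OR fell from 0.49–0.53 to 0.46–0.47, and from 0.66–0.85 to 0.59–0.67 at 14 events. Power was almost unchanged.

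**The case against.** The strongest reply is that the harm for AF is small. With 10 to 20 candidates the table's bias is 1% to 4%, or at most 0.04 on the log scale against an SE near 0.5. Error rates are sound. The candidate list sits in an appendix not shown, and the model type is not named. The study calls itself exploratory, admits its small sample, and has a two-group difference as its primary outcome. Part of the SE rise is what adjusting a logistic model for real risk factors always does. In one simulation Firth gave −2% to −5%, about as large as the bias it removes at 10 to 20 candidates. All of this stands, and it limits the size of the point.

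It does not remove the point. The objection that this is detail left to an analysis plan fails, because the article states the rule: what passes P<.20 goes in. Nor is Firth a mere preference, since it lowered the spread of the estimate in both simulations and the overall error where that was computed.

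A reader might go further and infer four things that the document does not support.
- That the AF odds ratio is certain to be inflated. This depends on an unstated candidate count and model type.
- That some secondary models must be unusable. No counts are given, every woman has a 12-lead ECG and echocardiography, so these outcomes could outnumber AF. A dose entered as continuous has no empty dose group.
- That the sparse-data problem extends to the line "categorical variables will be compared using the chi-square test". That line concerns cases against non-cases and does not touch the dose estimate.
- That a strict one-term-per-ten-events cap, or adjustment for age only, is needed. Ten per parameter allows 27.5/10 = 2.75 parameters, too few for the three kinds of confounder the Discussion names.

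**Conclusion.** The point holds as a moderate one. Tying the adjustment set to an uncapped P<.20 screen leaves roughly 3 to 9 events per parameter at about 27.5 AF events. It widens the interval for the dose effect, and may move the estimate away from the null by about 1% to 12% for AF. If a secondary outcome has only about 8 to 14 events, the shift could reach about 20%, with up to about 4% of fits failing. Tests and intervals keep close to their nominal levels, and no inflation was seen where there is no dose effect.

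These sizes rest on assumptions: maximum-likelihood logistic regression, 10 to 30 independent candidates, a true OR of 3.0, and the assumed counts for secondary outcomes. Under the Abstract's 15%, events rise to 35 and the problem eases.

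**What to change.** Make two changes to the Planned Statistical Analysis before analysis starts in June 2026.

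1. Name the model. If it is logistic, fit all AF and other-cardiac-disease dose models with the Firth penalty and profile-likelihood intervals, which SAS 9.4 PROC LOGISTIC offers.
2. Replace the P<.20 screen as the source of adjustment terms with a short set fixed in advance. Build it on age, comorbidities and chemotherapy, and keep it in proportion to the expected events. As a guide and not a strict cap, five events per parameter allows 27.5/5 = 5.5 parameters, so dose plus about four terms. At 35 events it allows 7, so dose plus six. The univariate results can still be reported as the description of non-radiation risk factors that the primary objective calls for.

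Reconciling the 10% and 15% planning rates would settle the event count used here.

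The cost is one model option and a few sentences. Estimates shrink slightly, and fewer factors are adjusted for at once, so a real confounder outside the set would be missed. Choosing the set on clinical grounds in advance limits that risk.

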## Discussion

### Summary

This study protocol aims to evaluate the risk of AF in patients with BC who have undergone RT, addressing a critical gap in understanding cardiovascular complications of BC treatment. AF is a common arrhythmia with potential to cause severe complications, and its risk may be heightened by the incidental cardiac radiation exposure during RT for BC. Given the increasing survival rates in patients with BC, assessing long-term cardiovascular outcomes has become essential for optimizing post-treatment care.

Several studies have investigated the association between RT for BC and AF [6,26,62]; however, these studies have not provided precise dosimetry data for cardiac substructures, and it remains unclear whether this association is causative or whether cancer and AF just share the same pathophysiologic mechanisms. Our study aims to enhance our understanding of how radiation dose distribution across specific cardiac regions correlates with AF incidence. Our study’s approach involves detailed dosimetry analysis of cardiac substructures using deep learning–based autosegmentation, including the left and right atria, the left and right ventricles, coronary arteries, the conduction system, and PVs. This precision in quantifying radiation doses received by these areas will allow for a more granular assessment of radiation exposure and its impact on AF risk, distinguishing our study from studies that have evaluated whole-heart doses [26]. Univariate and multivariable regression analyses will be used to isolate the effects of these localized radiation doses, while adjusting for confounding factors, such as age, comorbidities, and chemotherapy. This will provide an understanding of the dose-response association and help identify high-risk cardiac regions.

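### The P<.20 univariate screen leaves adjustment for age, comorbidities and chemotherapy in the dose–AF models to chance

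*Protocol article*

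**What the plan says.** All references are to the protocol article.

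- **Planned Statistical Analysis** describes two steps. Univariate regressions first look for individual and medical factors associated with each cardiovascular outcome. The threshold sentence reads, from the decimal onward, "20 will be retained for multivariable analyses [61", so the cut is P<.20. The dose analyses then use "regression models adjusted for the risk factors identified in the univariate analysis". Each dosimetry parameter gets its own model. No covariate is named as always included.
- **Discussion, Summary** says that the regressions will isolate the effects of local doses "while adjusting for confounding factors, such as age, comorbidities, and chemotherapy".
- **Sample Size Calculation** says "The required number of patients was set to 200", "based on a statistical power of 80"%, with "theoretical percentages of AF incidence of 10% for the group of patients considered moderately exposed" and 25% for the highly exposed. The groups are cut at the 75th percentile of heart dose.
- **Abstract, Results** gives about 15%, not 10%, for the moderately exposed group.

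**The concern.** A confounder is related both to cardiac dose and to AF. The screen looks only at the crude relation with AF and ignores the relation with dose. It has two weaknesses in this study.

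1. With few events, the crude test has limited power even at the lenient .20 level, so real confounders can be left out.
2. A factor that raises AF risk but goes with lower dose has its crude association partly hidden. It is then more likely to be left out, although it is one that matters for the dose estimate.

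The adjustment set is also unknown until the outcome data have been looked at, and intervals from the final model take no account of the selection. The dose–AF contrast is observational, and the Introduction hopes to use dosimetry to move towards a causal reading. Control of confounding therefore matters to the study's own aim.

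**Working it through.** **Step 1. The plan's own sample size.** Inputs: 10% vs 25%, power 80%, "with a type I error rate of 5"%, and two-sided tests ("All tests will be bilateral, with α=5"%). With k = n_high/n_moderate and pooled proportion p̄:

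n_moderate = [1.960·√((1+1/k)·p̄(1−p̄)) + 0.842·√(p₁(1−p₁) + p₂(1−p₂)/k)]² / (p₂−p₁)²

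- Equal groups (k=1, p̄=0.175): (1.053 + 0.443)²/0.0225 = 99.5, so 100 per group and 200 in total. This reproduces the stated figure.
- The 3:1 split that a 75th-percentile cut produces (k=1/3, p̄=0.1375): (1.350 + 0.680)²/0.0225 = 183.1, so 184 + 62 = 246.

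That mismatch is a separate matter, and nothing below depends on it. What follows takes N=200 as given.

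**Step 2. Expected events.** The cut gives 150 moderately and 50 highly exposed patients.

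- Methods rates: 150×0.10 + 50×0.25 = 15 + 12.5 = 27.5 events (13.75%).
- Abstract rate: 150×0.15 + 50×0.25 = 22.5 + 12.5 = 35 events (17.5%).

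**Step 3. Chance that a true risk factor fails P<.20.** The confounder strengths are assumptions. For a continuous factor standardised to SD 1, the test statistic is roughly normal with mean δ = ln(OR)·√(N·p(1−p)). The factor is dropped when |Z| < 1.282:

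P(drop) ≈ Φ(1.282−δ) − Φ(−1.282−δ)

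At 27.5 events, √(200×0.1375×0.8625) = 4.870. At 35 events, √(200×0.175×0.825) = 5.374.

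| OR per SD | δ, 27.5 events | P(drop), formula | P(drop), simulation | δ, 35 events | P(drop), formula |
|---|---|---|---|---|---|
| 1.2 | 0.888 | 64% | 63% | 0.980 | 61% |
| 1.3 | 1.278 | 50% | 49% | 1.410 | 45% |
| 1.5 | 1.975 | 24% | 25% | 2.179 | 19% |
| 2.0 | 3.376 | 2% | 3% | 3.725 | 1% |

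For a yes/no factor with 20–50% prevalence (chemotherapy, a comorbidity), simulation at 27.5 events gives a drop rate of about 61–62% at OR 1.5 and 35–39% at OR 2.0.

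Masking: with OR 1.5 per SD, correlation −0.3 with dose and a true dose OR of 3, simulated drop rates are about 46–48%, against about 25% without masking.

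**Step 4. Effect on the dose estimate.** These are simulations with N=200, 13.75% AF and top-quartile exposure, comparing the screen with a fixed confounder set. Strengths, correlations and dependence among confounders are all assumed.

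| Assumed confounding | True dose OR | Median OR, screen | Median OR, fixed set |
|---|---|---|---|
| One, OR 1.5, r=0.3 | 1 | 1.05 | 1.02 |
| One, OR 1.5, r=−0.3 | 3 | about 2.8 | about 3.0 |
| Three, OR 1.5, r=−0.15 | 3 | 2.88 | 3.04 |
| Five weak, with dose | 1 | 1.02–1.18 | about 1.0 |
| Five weak, against dose | 3 | about 2.1–2.5 | 3.0–3.1 |

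In the last row power is about 32–44% with the screen and 50–52% with the fixed set. The 2.1 end needs five mutually independent confounders, each with r=0.3 in size and all acting on dose in one direction. Together they would explain 5×0.3² = 45% of the variance in dose. Other dependence structures gave 3.0 to 2.5 or 3.1 to 2.8. Type I error stayed at 4–6% in the null scenarios.

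**The case against.** **The Discussion sentence is illustrative.** It introduces its list with such as, and it names univariate and multivariable regression, which is the Methods procedure. A reader might infer a flat contradiction between the two sections. The documents do not support that, because the listed factors can be read as candidates for the screen. What stands is that the Discussion presents the adjustment as planned and the Methods rule does not guarantee it.

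**A drop rate is not a bias.** Factors that fail a .20 screen tend to be weakly associated in the sample at hand. With one confounder the bias is small, and a strong age effect would usually survive. This stands, and it limits the size of the point.

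**The masking mechanism has no documented instance.** Nothing in the article says that older women, or women with comorbidities, received lower heart doses. Restricting enrolment to women from about 65 also narrows the age range. Masking is a possibility here, not something shown.

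**The study is exploratory and sized on two crude percentages.** That is true. Even so, the article's Conclusions expect dose–risk associations to improve radiotherapy delivery, and the adjusted models are the ones that would inform this.

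**Conclusion.** The point holds as a weakness in a rule that the protocol itself fixes, so it is not a detail left to an analysis plan. Covariate selection for the dose models depends on outcome-only tests with about 27.5 expected events (35 under the Abstract's rate). Continuous confounders of moderate strength would be missed about 25–50% of the time, and yes/no factors of OR 1.5 more often than that. The adjustment described in the Discussion is therefore not assured.

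The consequence for the dose estimate is known only as a range, because the documents give neither confounder strengths nor dose correlations. It runs from negligible with one confounder to a marked attenuation and loss of power when several weak confounders all run against dose.

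Two stronger readings do not hold. The screen does not visibly inflate false positives, since type I error stays near 5%. Nor is a fall from about 3.1 to 2.1 the expected loss; it is the extreme of the scenarios examined.

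**What to change.** In Planned Statistical Analysis, replace the P<.20 rule for the dose models with one short covariate set, fixed before outcome data are examined and used in every dose model. The natural set is what the Discussion already names: age, one comorbidity or cardiovascular-risk summary, and chemotherapy (yes/no). Keep the univariate screen only for describing nonradiation risk factors, which is a separate part of the primary objective.

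The change takes about two sentences. Dose plus three single-parameter covariates makes four parameters: 27.5/4 ≈ 6.9 events per parameter (35/4 ≈ 8.8 under the Abstract's rate). A Firth-penalised logistic fit is a sensible option at that level. Some precision is spent on covariates that may turn out not to matter. A longer list is harder to defend: dose plus five covariates leaves 27.5/6 ≈ 4.6 events per parameter.
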